### 9.4.3. Pharmacokinetic Analysis

#### 9.4.3.1. Single Dose and Steady-State PF-07248144 Pharmacokinetic Analysis (With the Exception of Food Effect Assessment) [REDACTED]

Following single dose administration, plasma PK parameters including the  $C_{max}$ ,  $T_{max}$ ,  $AUC_{last}$ , and if data permit,  $AUC_{inf}$ ,  $CL/F$ ,  $V_z/F$ , and  $t_{1/2}$  will be estimated. Following multiple doses, steady state PK parameters including  $C_{max,ss}$ ,  $T_{max,ss}$ ,  $AUC_{\tau,ss}$ ,  $C_{min,ss}$ ,  $CL_{ss}/F$ , and if data permit,  $V_{ss}/F$ ,  $t_{1/2}$ , and  $R_{ac}$  ( $AUC_{\tau,ss}/AUC_{\tau,sd}$ ) will be estimated.

The single-dose and steady-state PK parameters will be summarized descriptively (n, mean, standard deviation, CV, median, minimum, maximum, geometric mean and its associated CV) by dose, cycle and day.

PF-07248144 concentrations will be summarized descriptively (n, mean, standard deviation, CV, median, minimum, maximum, geometric mean and its associated CV) by dose, cycle, day and nominal time. Individual participant and median profiles of the concentration-time data will be plotted by dose, cycle and day (single dose and multiple-dose) using nominal times. Individual and median PK profiles will be presented on both linear and log-linear scales for drug concentrations.

Dose normalized  $C_{max}$ ,  $AUC_{last}$ ,  $AUC_{\tau}$  (at steady state) and  $AUC_{inf}$  (if estimated), and will be plotted against dose (using a logarithmic scale) by cycle and day. These plots will include individual patient values and the geometric means for each dose. These plots will be used to help understand the relationship between the PK parameters and dose.

The observed accumulation ratio will be summarized descriptively.

[REDACTED]

#### **9.4.3.5. Pharmacodynamic and Biomarker Analyses**

Results from PD and biomarker exploratory analyses will be reported in the CSR where possible. However, given the exploratory nature of exploratory objectives and endpoints, the analyses may not be complete at the time of the CSR. Results from exploratory analyses that are not included in the CSR will be shared with the scientific community through publication at a scientific conference and/or in a peer-reviewed scientific journal.

[REDACTED]

[REDACTED]

#### **9.4.5. Safety Analyses**

All safety analyses will be performed on the safety population.

Summaries and analyses of safety parameters will include all participants in the safety analysis set.

AEs, ECGs, BP, pulse rate, continuous cardiac monitoring, and safety laboratory data will be reviewed and summarized on an ongoing basis during the study to evaluate the safety of participants. Any clinical laboratory, ECG, BP, and PR abnormalities of potential clinical concern will be described. Safety data will be presented in tabular and/or graphical format and summarized descriptively, where appropriate.

Medical history and physical examination and neurological examination information, as applicable, collected during the course of the study will be considered source data and will not be required to be reported, unless otherwise noted. However, any untoward findings identified on physical and/or neurological examinations conducted during the active collection period will be captured as AEs, if those findings meet the definition of an AE. Data collected at screening that are used for inclusion/exclusion criteria, such as laboratory data, ECGs, and vital signs, will be considered source data, and will not be required to be reported, unless otherwise noted. Demographic data collected at screening will be reported.

#### 9.4.5.1. Electrocardiogram Analyses

Changes from baseline for the following ECG parameters: QT interval, heart rate, QTc interval, PR interval, and QRS complex will be summarized by treatment and time.

The number (%) of participants with maximum postdose QTc values and maximum increases from baseline in the following categories will be tabulated by treatment:

##### Safety QTc Assessment

| Degree of Prolongation | Mild (msec) | Moderate (msec) | Severe (msec) |
|------------------------|-------------|-----------------|---------------|
| Absolute value         | >450-480    | >480-500        | >500          |
| Increase from baseline |             | 30-60           | >60           |

In addition, the number of participants with uncorrected QT values >500 msec will be summarized.

If more than 1 ECG is collected at a nominal time after dose administration (for example, triplicate ECGs), the mean of the replicate measurements will be used to represent a single observation at that time point. If any of the 3 individual ECG tracings has a QTc value >500 msec, but the mean of the triplicates is not >500 msec, the data from the participant's individual tracing will be described in a safety section of the CSR in order to place the >500 msec value in appropriate clinical context. However, values from individual tracings within triplicate measurements that are >500 msec will not be included in the categorical analysis unless the average from the triplicate measurements is also >500 msec. Changes from baseline will be defined as the change between the postdose QTc value and the average of the time-matched baseline triplicate values on Day 1, or the average of the predose triplicate values on Day 1.

In addition, an attempt will be made to explore and characterize the relationship between plasma concentration and QT interval length using a PK/PD modeling approach. If a PK/PD relationship is found, the impact of participant factors (covariates) on the relationship will be examined.

The analysis of ECG results will be based on participants in the safety analysis set with baseline and on-treatment ECG data. Baseline is defined as Cycle 1 Day 1 predose.

ECG measurements (an average of the triplicate measurements) will be used for the statistical analysis and all data presentations. Any data obtained from ECGs repeated for safety reasons after the nominal time-points will not be averaged along with the preceding triplicates. Interval measurements from repeated ECGs will be included in the outlier analysis (categorical analysis) as individual values obtained at unscheduled time points.

QT intervals will be corrected for HR (QTc) using standard correction factors (ie, Fridericia's [default correction], Bazett's, and possibly a study specific factor, as appropriate). Data will be summarized and listed for QT, HR, RR, PR, QRS, QTcF (and other correction factors, eg, QTcB as appropriate), and by dose level in Part 1A and by group in Part 2 (Part 2A, [REDACTED]). Individual QT (all evaluated corrections) intervals will be listed by dose and time in Part 1A and by cohort and time in Part 2. The most appropriate correction factor will be selected and used for the following analyses of central tendency and outliers and used for the study conclusions. Descriptive statistics (n, mean, median, standard deviation, minimum, and maximum) will be used to summarize the absolute corrected QT interval and changes from baseline in corrected QT after treatment by study cohort, dose and time point. Details of additional analysis (if any) will be specified in SAP.

#### **9.4.5.2. Adverse Events**

AEs will be graded by the investigator according to the CTCAE version 5.0 and coded using MedDRA. AE data will be reported in tables and listings. Summaries of adverse event by mapped terms, appropriate thesaurus level, toxicity grade, and seriousness and relationship to study treatment will be presented, as well as summaries of adverse events leading to death and premature withdrawal from study treatment. The number and percentage of participants who experienced any AE, SAE, treatment related AE, and treatment related SAE will be summarized according to worst toxicity grades. The summaries will present AEs both on the entire study period and by cycle (Cycle 1 and Cycles beyond 1). Listings of DLTs and deaths will be provided.

#### **9.4.5.3. Laboratory Test Abnormalities**

The number and percentage of participants who experienced laboratory test abnormalities will be summarized according to worst toxicity grade observed for each laboratory assay. The analyses will summarize laboratory tests both on the entire study period and by cycle (Cycle 1 and Cycles beyond 1). For laboratory tests without CTCAE grade definitions, results will be categorized as normal, abnormal, or not done.

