- i) **Contraception Check:** The investigator or his or her designee, in consultation with the participant, will confirm that the participant has selected an appropriate method of contraception for the individual participant (and his or her partner[s]) from the permitted list of contraception methods and will confirm that the participant has been instructed in its consistent and correct use. The investigator or designee will inform the participant of the need to use highly effective contraception consistently and correctly and document the conversation and the participant's affirmation in the participant's chart (participants need to affirm their consistent and correct use of at least 1 of the selected methods of contraception). In addition, the investigator or designee will instruct the participant to call immediately if the selected contraception method is discontinued or if pregnancy is known or suspected in the participant or partner.
- j) **Concomitant Treatments:** All concomitant medications and nondrug supportive interventions should be recorded on the CRF.
- k) **Hematology, Blood Chemistry, Coagulation, and Urinalysis:** No need to repeat on C1D1 if baseline assessment is performed within 7 days prior to that date ([Section 10.2](#) for a complete list of clinical laboratory tests).
- l) **Pregnancy Test:** Pregnancy tests may be urine or serum tests, but must have a sensitivity of at least 25 mIU/mL. Pregnancy tests will be performed in WOCBP. Following a negative pregnancy test result at screening, appropriate contraception must be commenced and a second negative pregnancy test result will be required at the baseline visit prior to the participant's receiving the study intervention. Pregnancy tests will also be done whenever 1 menstrual cycle is missed during the active treatment period (or when potential pregnancy is otherwise suspected) and at the end of the study. Pregnancy tests may also be repeated if requested by IRBs/ECs or if required by local regulations (see [Section 10.2](#)).
- m) **PSA:** For prostate cancer only, PSA to be performed every 4 weeks from C1D1 (±2 days) until EOT.
- n) **Viral Disease Screening Tests:** HBsAg, , HBcAb, anti-HBs, HCVAb, and HIV to be conducted by local laboratory where required by local regulations or if warranted by participant history.
- o) **Registration:** Participant enrollment number and dose level allocation assigned by Pfizer Inc.

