| 
Part 2A: ER+HER2- breast cancer 2L+, monotherapy
 
 
To assess safety and tolerability of PF-07248144 monotherapy at the RDE from Part 1A in participants with advanced or metastatic 2L+ ER+HER2- breast cancer who have progressed after at least 1 prior line of CDK4/6 inhibitor and 1 line of endocrine therapy.
 
 
Part 2B: 2-4L ER+HER2- breast cancer, combination
 
 
To assess safety and tolerability of PF-07248144 at the RDE in combination with fulvestrant (determined in Part 1B) in participants with advanced or metastatic ER+HER2- breast cancer whose disease has progressed after 1 line of a CDK4/6 inhibitor and at least 1 line of endocrine therapy and who must not have received more than 3 lines of systemic therapies including up to 1 line of cytotoxic chemotherapy for visceral disease in advanced or metastatic setting.
 
 
[REDACTED]
 
[REDACTED]
 | 
 
AEs as characterized by type, frequency, severity (as graded by NCI CTCAE version 5.0), timing, seriousness, and relationship to study therapy.
 
Laboratory abnormalities as characterized by type, frequency, severity (as graded by NCI CTCAE version 5.0), and timing.
 
 |

| Part 2: PF-07248144 Monotherapy (Part 2A) and Combinations in Dose Expansion (Parts 2B [REDACTED])                                                                                                                                                                                                                     |                                                                                                                                                                                                                                                                                                                                                                                                                                                                                        |

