  - Cessation of regular menses for at least 12 consecutive months with no alternative pathological or physiological cause; [status may be confirmed with/and have] a serum follicle-stimulating hormone (FSH) level confirming the post menopausal state;
  - Have undergone a documented hysterectomy and/or bilateral oophorectomy;
  - Have medically confirmed ovarian failure. All other female participants (including female participants with tubal ligations) are considered to be of childbearing potential.
8. Participants must have at least 1 measurable lesion as defined by RECIST version 1.1 that has not been previously irradiated.
9. ECOG Performance Status PS 0 or 1 (See [Appendix 12: Section 10.12](#)).
10. Adequate Bone Marrow Function, including:
  - a. ANC  $\geq 1,500/\text{mm}^3$  or  $\geq 1.5 \times 10^9/\text{L}$ ;
  - b. Platelets  $\geq 100,000/\text{mm}^3$  or  $\geq 100 \times 10^9/\text{L}$ ;
  - c. Hemoglobin  $\geq 9 \text{ g/dL}$ .
11. Adequate Renal Function, including:
  - a. Serum creatinine  $\leq 1.5 \times \text{ULN}$  or estimated creatinine clearance GFR  $\geq 60 \text{ mL/min}$  ( $\geq 50 \text{ mL/min}$  for Part 2 dose expansion is acceptable) as calculated using the method standard for the institution. In equivocal cases, a 24 hour urine collection test can be used to estimate the creatinine clearance more accurately.

12. Adequate Liver Function, including:

- a. Total serum bilirubin  $\leq 1.5 \times$  ULN unless the participant has documented Gilbert syndrome;
  - b. AST and ALT  $\leq 2.5 \times$  ULN; AST and ALT  $\leq 3.0 \times$  ULN if there is liver involvement by the tumor for Part 1 dose escalation. AST and ALT  $\leq 5.0 \times$  ULN if there is liver involvement by the tumor for Part 2 dose expansion.
13. Resolved acute effects of any prior therapy to baseline severity or CTCAE Grade  $\leq 1$  except for AEs not constituting a safety risk by investigator judgment.
14. Participants who are willing and able to comply with all scheduled visits, treatment plan, laboratory tests, lifestyle considerations, and other study procedures.
15. Capable of giving signed informed consent as described in [Section 10.1.3](#), which includes compliance with the requirements and restrictions listed in the ICD and in this protocol.

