## **2.4. Safety Endpoints**

For safety summaries, unless other specified, safety data are summarized for the data collected during “on-treatment period”, which is defined as the period that starts with the first dose date and ends at min(last dose date + 28 days, start of new anti-cancer therapy – 1 day). Anti-cancer radiation or surgery is not considered as a start of new anti-cancer therapy.

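### Laboratory abnormalities, a primary endpoint, are tabulated by worst observed grade with no comparison to the entry grade, so low-grade rows can include abnormalities that only persist from entry

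*Protocol*

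**What the plan says.** Section 3 of the protocol lists this among the primary endpoints for Parts 1 and 2: "Laboratory abnormalities as characterized by type, frequency, severity (as graded by NCI CTCAE version 5.0), and timing".

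Protocol 9.4.5.3 gives the tabulation rule: "The number and percentage of participants who experienced laboratory test abnormalities will be summarized according to worst toxicity grade observed for each laboratory assay". It asks for this over the whole study and separately for Cycle 1 and later cycles. For ungraded tests it says: "For laboratory tests without CTCAE grade definitions, results will be categorized as normal, abnormal, or not done".

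SAP 5.2.2 keeps the worst-grade rule, drops the split by cycle, and replaces the categories for ungraded tests with high, normal and low. Neither section mentions the baseline grade, a new-or-worsened count or a shift table. The SAP mentions shift tables only for vital signs (5.2.3), and there only if judged necessary.

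Other relevant text:

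- Inclusion criterion 10 (Protocol 5.1), headed "Adequate Bone Marrow Function, including", accepts hemoglobin from 9 g/dL and platelets from 100,000/mm3.
- SAP 2.4 limits safety summaries to the on-treatment period, "which is defined as the period that starts with the first dose date".
- Protocol 9.4.5 says that screening data used for eligibility, "such as laboratory data, ECGs, and vital signs, will be considered source data, and will not be required to be reported"; the sentence then allows for exceptions noted elsewhere.
- Table 1, footnote k, says of hematology, chemistry, coagulation and urinalysis: "No need to repeat on C1D1 if baseline assessment is performed within 7 days prior to that date". Table 3 has the same footnote for Part 2.

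**The concern.** A worst-grade table without a baseline reference answers the question of who had an abnormal value at some point on treatment. A safety reader wants to know who became abnormal, or more abnormal, on treatment. The two counts differ by the participants who entered with an abnormality that persisted without worsening.

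The cohorts have no control group that would reveal the difference, and the entry values are not assured of being reported. The rows at risk matter for this drug, whose reported toxicity is mainly hematologic. In Protocol 2.2.4, treatment-related anemia was reported in 24 of 59 participants at any grade and in 6 of 59 at Grade 3 or higher, which leaves 24 - 6 = 18 of 59 at Grade 1-2. Those are adverse event counts and not laboratory rows, but they show that low grades carry much of the anemia profile.

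**Working it through.** The plan states no figure for this point, so there is nothing to reproduce. The check is first textual, then one line of arithmetic.

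**Can an entry abnormality reach the table?**

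1. *Eligibility.* Hemoglobin from 9 g/dL and platelets from 100,000/mm3 are accepted. The documents give no reference ranges; I take it that values at these limits lie below normal. AST and ALT up to 5 x ULN are also accepted in Part 2 with liver involvement, but the documents do not settle how those are graded against an abnormal baseline, so nothing here rests on them.
2. *On-treatment window.* It removes screening samples taken before the first dose date. An unchanged entry abnormality is still there at the first scheduled draw after Day 1: Day 8 in Part 1 (Table 1) and Day 15 in Part 2 (Table 3). It is then the worst grade observed, or part of it.
3. *Visibility of the entry value.* SAP 2.3.3 defines baseline as the last value before dosing. When the C1D1 sample is skipped under footnote k, that is the screening value, which falls under the reporting exemption in Protocol 9.4.5.
4. *Contrast within the plan.* ECG parameters are analyzed as changes from baseline (Protocol 9.4.5.1), and a DLT must be a clinically significant shift from baseline (Protocol 4.3.5). The laboratory endpoint has no such reference.

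**How much does each case add?**

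Let n be the cohort size and k the number of participants who enter with an abnormality on a given assay that persists on treatment without worsening. The any-grade row under the stated rule exceeds the new-or-worsened count by k participants, that is, by 100k/n percentage points.

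- Expansion cohort, n = 30 (Protocol 9.2.2): 100 x 1/30 = 3.3 points per participant, so 3.3k points in all.
- Part 1B, n = 9 to 6 (Protocol 9.2.1): 100 x 1/9 = 11.1 points to 100 x 1/6 = 16.7 points per participant.

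The documents do not give k. At k = 0 the two counts agree; as an assumed range, k = 3 gives 10 points and k = 6 gives 20 points in a cohort of 30.

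For assays with an entry limit, the limit keeps severe values out at entry, so the excess in the Grade 3-4 rows is about 0. Assays without an entry limit, such as lipase or phosphate, do not have that protection.

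**The case against.** The strongest reply is that this is an absent table and not an error. The endpoint asks for type, frequency, severity and timing; it does not say new, worsened or treatment-emergent, and a worst-grade table delivers what it asks for. Protocol 9 leaves further detail to the SAP, where shift tables usually live. Worsening is also picked up elsewhere: clinically relevant laboratory changes go to the adverse event page (Protocol 8.2.4), worsening from baseline can qualify as an adverse event (Protocol 10.3.1), and adverse events are summarized by grade and relationship.

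Part of this stands. Nothing is contradicted, and the study is descriptive with no hypothesis test. But the protocol does state the tabulation rule, and SAP 5.2.2 keeps it without adding a baseline comparison. Adverse event reporting depends largely on the investigator judging a change clinically significant, so it does not correct the laboratory rows.

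Several stronger readings are tempting and should not be drawn:

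- *That the low-grade rows will in fact reflect who was enrolled.* They can; without a baseline prevalence no one can say that they will.
- *That entry values will go unreported.* The exemption covers only screening data used for eligibility and allows exceptions. C1D1 samples are scheduled separately unless baseline was taken within the preceding 7 days.
- *That a predose sample on C1D1 will be counted as on-treatment.* The window opens by date, so it does not by itself exclude one, but this depends on programming.
- *That a persisting abnormality is counted once per cycle period, or that ungraded tests are only normal or abnormal.* Both describe Protocol 9.4.5.3; SAP 5.2.2 drops the cycle split and separates high from low.

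**Conclusion.** The point holds as a limited one. The stated rule for a primary endpoint does not separate abnormalities that persist from entry from those that appear or worsen on treatment, and nothing else in the protocol or SAP makes that separation in the laboratory tables. It affects the any-grade and Grade 1-2 rows, by 3.3 points per affected participant in a cohort of 30 and by 11.1 to 16.7 points in Part 1B. The total is unknown and could be zero. The conclusion assumes only that some participants enter at the permitted low hemoglobin or platelet values and stay there.

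A reader might infer that dose selection or the DLT assessment is compromised. The documents do not support that: DLTs already require a shift from baseline, and Grade 3-4 rows for assays with entry limits are largely unaffected. This is a worthwhile, inexpensive improvement to how the safety profile is read.

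**What to change.** In Protocol 9.4.5.3 and SAP 5.2.2:

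1. Keep the worst-grade table, but restrict it to samples drawn after the first dose, by time where the dates coincide.
2. Add the number and percentage of participants whose worst post-baseline grade is higher than their baseline grade. Use the SAP 2.3.3 baseline, which is the screening value when C1D1 is not repeated.
3. Add a table of baseline grade by worst post-baseline grade for each assay, by dose level in Part 1 and by cohort in Part 2. For tests without CTCAE grades, use the SAP's high, normal and low categories.

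The cost is a sentence in each document, one extra count and one shift table per assay, all from data already collected. The only downside is a small amount of additional tabulation.
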